### Study type and design

This study will be a randomized controlled, crossover, 3-arm, clinical trial. The protocol description followed the SPIRIT [40] and the TIDieR [41] guidelines (Fig 1 and S1–S3 Tables). Participants will undergo a health history questionnaire, anthropometric measures which include height, body mass, waist circumference and body composition, a period of familiarization and strength assessment. At least 4 days after the strength tests, they will carry out 3 randomized experimental sessions, separated by at least 4 (but no more than 28) washout days, as it has been shown that the acute effect of exercise on improved insulin action lasts up to 2 days [42]. In case the sessions are scheduled 21 to 28 days apart, participants will be required to perform a familiarization session 2 weeks after the preceding (and 1 to 2 weeks before the following) experimental session to avoid defamiliarization. The interval between experimental sessions will be recorded and reported in the final manuscript, and discussed accordingly. To avoid the variation in insulin sensitivity across the menstrual cycle [43–49], in case premenopausal women are included in the sample, they will be assessed in the follicular phase (days 1–14) [9, 26, 50–52] of their menstrual cycle. Two of the experimental sessions will be performed with strength exercises: a high-volume session [3 sets per exercise–high volume]; a low-volume session [1 set per exercise–low volume]; and a control session: no exercise. In the exercise sessions, 7 exercises will be performed for the major muscle groups (1 –hex bar squat; 2 –bench press; 3 –leg press; 4 –lat pulldown; 5 –leg extension; 6 –shoulder press; 7 –leg curl; Fig 2), totaling 21 sets in the high-volume session and 7 sets in the low volume session [24]. The sessions will be held at night, between 8:00 pm and 9:00 pm. This time schedule for the sessions is ecologically valid, as exercise in the evening is commonly observed in fitness centers due to time constraints for exercising earlier during the day [13, 53], and it has been shown that night-time exercise does not affect sleep duration or quality [53]. The next morning between 7:00 am and 8:00 am (between 10 and 11 hours after the session), an OGTT will be performed in a local clinical laboratory. Participants will respond to scales of feeling, enjoyment, and self-efficacy after the exercise sessions. All sessions will be supervised by a certified fitness professional. The experimental design is illustrated in Fig 3.

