### Random allocation

The order in which the experimental sessions will be held will be randomized with the aid of the website https://www.randomizer.org. The random orders generated by the program will be printed and inserted inside opaque, sequentially numbered envelopes, which will later be sealed by a research collaborator not directly involved in data collection. After completing the strength tests, the envelope will be opened, and the sequence of experimental sessions that will be followed will be revealed.

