### Dietary control

Participants will be instructed by a certified nutritionist on how to log their diet in a notebook on 3 nonconsecutive days of the week, one of the days being on the weekend [56]. Daily caloric intake in kilocalories (kcals) and kcals consumed from lipids, protein and carbohydrates will be analyzed using nutritional software (Dietbox Software, Brazil). Thereafter, a food plan will be given to the participants who will follow exactly the same food plan the day before and the day of the experimental sessions. This food plan will not change the composition and amounts of the daily basis food consumption of the participants, but they will be instructed to consume the same meals and the same amounts of food at the same hours of the day during the experimental protocol days, including a pre-session meal composed of 65% carbohydrates, 15% proteins, and 20% lipids one hour before reporting to the gym (~6:30 pm). Frequent text messages will be sent to participants to ensure they followed instructions. Adherence to dietary instructions will be verified by assessing their food record. After the experimental sessions, a standard snack (65% carbohydrates, 15% proteins, and 20% lipids) will be offered, which will be ingested between 9:00 and 9:30 pm at the gym where the sessions will take place, with calories determined from the individual daily needs, plus the estimated net energy expenditure of the session [57]. Participants will be instructed not to consume food after the offered snack and must fast until the morning of the next day to perform the OGTT in a local laboratory.

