### Interventions

Participants will be instructed not to perform moderate/high physical activity during the 48 hours that precede the experimental sessions. Frequent text messages will be sent to participants to ensure they follow instructions. Adherence to physical activity instructions will be verified before each session by asking the participants.

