#### Weaknesses

This study cannot be completed in a double-blind manner, as the participants and the researchers who will be present during the sessions will be aware of the treatment (high- or low-volume or control session). However, the professionals at the clinical lab who will collect and analyze the blood will be blinded to treatment, as well as the researcher who will perform the statistics. We will include obese men and women over 40 years old, so our results might not be readily translated to other clinical populations, such as younger, healthy individuals or individuals living with DM2. Furthermore, individuals with potentially different levels of insulin resistance might be included in this study, and greater exercise-induced improvement in insulin resistance has been observed in individuals with higher levels of baseline insulin resistance [26, 92]. Thus, this factor can also increase results variability. However, it should be pointed out that studying overweight/obese subjects regardless of their insulin resistance levels or fasting glucose impairment status is commonplace in the related literature [8, 93–95]. Nevertheless, the fact that participants will be their own control minimizes this potential source of variability. Moreover, individual results will be presented and discussed accordingly should individual levels of insulin resistance affect average group results. Furthermore, DM2 patients will be excluded, following our exclusion criteria. Also important to point out, participants might not follow the dietary and physical activity instructions the day before and the day of the sessions, which might also be confounding factors when interpreting our results. However, we will stress the importance of following these instructions by sending frequent text messages, and adherence will be verified when they report to the gym, and we will ask them to report what they ate to the nutritionist, which we believe increases adherence to diet prescription. Finally, per our study design, we will assess two significantly different strength exercise volumes, and by default time commitment, as lack of time is usually listed as one of the main reasons not to adhere to exercise [30]. Thus, our study design is not intended to explore a potential dose-response relationship between strength exercise volume and improvements in insulin sensitivity, although this approach would bear practical implications.

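### The full session order is opened at least 4 days before session 1 although no stated step before arrival needs it; opening one envelope per session at the gym would cheaply reduce a plausible, unquantified bias.

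*Protocol article*

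**What the plan says.** Random allocation states that, once the strength tests are finished, "the envelope will be opened, and the sequence of experimental sessions that will be followed will be revealed". The opening is a single event covering all three sessions.

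Study type and design sets the timing: "At least 4 days after the strength tests, they will carry out 3 randomized experimental sessions", and the sessions are "separated by at least 4 (but no more than 28) washout days".

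The requirements before arrival are common to all conditions. Under Dietary control, participants "will follow exactly the same food plan the day before and the day of the experimental sessions", with a fixed-composition meal one hour before they report to the gym. Under Interventions: "Participants will be instructed not to perform moderate/high physical activity during the 48 hours that precede the experimental sessions". High-volume session sets arrival at 7:30 pm, rest until 8:00 pm, and the pre-session feeling scale during that rest. Low-volume session and Control session are described as identical apart from the exercise itself and, for low volume, a start at 8:35–8:40 pm. For the control, the pre-session instructions are expressly the same.

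On checking adherence: "Adherence to physical activity instructions will be verified before each session by asking the participants". Diet is checked from the participant's food record. Weaknesses concedes that "participants might not follow the dietary and physical activity instructions the day before and the day of the sessions", and that this may confound interpretation. It does not connect such lapses with knowing which session is coming.

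**The concern.** An exercise session cannot be hidden from the person doing it, and Blinding procedures says so. That explains why participants know the condition during a session. It does not explain why the condition should be known days beforehand.

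A crossover removes stable differences between people. It does not remove behaviour that changes with the condition a person expects. Someone who knows that tomorrow brings 21 sets, 7 sets or none may eat, rest or attend differently. Four things are exposed:

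- **Primary outcome.** Diet and activity on the day before and the day of a session can affect the next-morning glucose tolerance test. Lapses unrelated to condition mostly add noise; lapses that follow the condition bias the comparison.
- **Secondary outcome.** The feeling scale is taken before and after each session. If the order is known, the pre-session score may already contain anticipation of the session.
- **Attendance.** The plan expects 25–40% loss, reschedules missed sessions, and discontinues anyone whose interval exceeds 28 days. Postponing an unwelcome session that is known in advance could end in dropout.
- **Analysis.** Data analysis keeps non-adherers in the intention-to-treat analysis. The per-protocol analysis excludes them, but only where the deviation is recorded.

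**Working it through.** No figure in the plan bears on this point, and the sample-size calculation is unaffected. The check is to ask which steps need the order and when it becomes known.

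**1. Lead time (Study type and design).**
- Session 1: known at least 4 days ahead.
- Session 2: at least 4 + 4 = 8 days.
- Session 3: at least 4 + 4 + 4 = 12 days, and at most 28 + 28 = 56 days plus the lead time to session 1, for which no upper limit is stated.

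The 48-hour activity window and the two diet days before every session therefore fall after the reveal.

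**2. Does any step need the order?**

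| Step | Section | Differs by condition? |
|---|---|---|
| Food plan, day before and day of session | Dietary control | No |
| Meal one hour before arrival (about 6:30 pm) | Dietary control | No, if arrival is common |
| 48-hour activity restriction, reminders | Interventions | No |
| Arrival at 7:30 pm | High-volume session | Implied common; not restated for low volume |
| Pre-session instructions | Control session | No |
| Pre-session feeling score | High-volume session | No |
| Start time | Low-volume session | Yes, after arrival |
| Number of sets | Low-volume and Control sessions | Yes, after arrival |
| Snack size | Dietary control | Yes, eaten 9:00–9:30 pm |

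Every step that clearly depends on the order comes after arrival. The uncertain row is arrival for low volume. With a common 7:30 pm arrival, the wait is 65 to 70 minutes (7:30 to 8:35–8:40), against 30 minutes for high volume. If arrival were moved instead, the meal would move with it and the schedule would itself disclose the condition.

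**3. Room for a later reveal.** Arrival is at 7:30 pm and the high-volume session starts at 8:00 pm. The adherence check, the feeling score and the opening must fit in those 30 minutes. From 8:00 pm to the earliest snack time of 9:00 pm leaves at least 60 minutes to portion the snack.

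**4. Sessions known with certainty before arrival.**
- As written: 3 of 3 per participant, i.e. 3 × 14 = 42 of 42 for 14 completers, or 3 × 20 = 60 of 60 if all 20 recruits attended every session.
- One envelope per session: 1 of 3, i.e. 14 of 42, or 20 of 60. Session 1 has three possibilities, session 2 has two, and session 3 follows by elimination.

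**5. Size of the bias.** It would depend on how far behaviour shifts with the expected condition and how far that shift moves the outcome. The document gives neither, so no estimate is offered.

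**The case against.** The strongest reply is that disclosure to participants is inferred. Random allocation does not say to whom the order is revealed, and a condensed article may leave that to the full protocol. This stands as a limit on certainty. Nothing says the order is withheld, however, and Blinding procedures states that participants cannot be blinded, so disclosure is the natural reading.

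Second, some steps do depend on the order: the snack includes the energy the session is estimated to cost, and the low-volume session starts later. This also stands, but both come after arrival, and staff could prepare for them that evening.

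Third, the plan already works against the problem. It uses one food plan based on habitual intake, nutritionist instruction, reminders, food records, a question about activity, rescheduling and a per-protocol analysis. These reduce the risk. They do not remove it, because undeclared lapses pass through all the adherence checks and the per-protocol exclusions rest on the same reports. Blinding of the laboratory staff and the analyst protects measurement and analysis, not behaviour before the session.

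Fourth, the remedy is partial: the third session can always be deduced. That is correct.

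A reader might go further and infer that allocation concealment fails or that the results will be biased. The documents support neither. The envelopes are opaque, numbered and sealed by someone not directly involved in data collection, and they are opened only after the strength tests, so concealment up to enrolment is intact. No passage shows that behaviour will change.

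**Conclusion.** The point holds as a cheap improvement. The plan fixes a single early reveal that no stated participant step before arrival requires, and this leaves open a route to condition-dependent diet, activity, attendance and pre-session feeling scores. The bias is plausible, with unknown size and direction. What can be counted is the exposure: 3 of 3 sessions are known before arrival as written, against 1 of 3 with a session-by-session reveal.

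This rests on two assumptions that the article does not settle: that participants are told the order when the envelope is opened, and that arrival is at 7:30 pm for the low-volume session too. It might also be inferred that foreknowledge is wholly avoidable. It is not, since the last session follows from the first two and the second is narrowed to two options. No contradiction, wrong figure or invalid analysis is involved, and sample size, power and significance level do not change.

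**What to change.** Under Random allocation, replace the single envelope with three sealed, opaque, numbered envelopes per participant, one per session. At each visit, open the relevant one at the gym after the diet and activity check and the pre-session feeling score have been recorded, and before any condition-specific guidance. High-volume session currently lists exercise guidance alongside the feeling scale, so state that the scale comes first.

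State who learns the allocation and when. Confirm the arrival time for the low-volume session and keep it the same for all conditions. Use the same reminder texts for every session.

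The cost is two more envelopes per participant (2 × 20 = 40 for 20 recruits) and portioning the snack the same evening. If the full protocol already withholds the order from participants until each session, one sentence saying so would be enough.

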### Blinding procedures

Due to characteristics inherent to this trial (exercise), blinding of participants and researchers involved in data collection is not possible. However, employees from the local clinical laboratory responsible for blood harvesting, processing, and analysis will be blinded to allocation. For that, participants will be instructed not to reveal details about the protocol to the clinical laboratory personnel. Moreover, the researcher responsible for data analysis will remain blind to allocation until completion of analysis (see below in *Data analysis*).

### Dietary control

Participants will be instructed by a certified nutritionist on how to log their diet in a notebook on 3 nonconsecutive days of the week, one of the days being on the weekend [56]. Daily caloric intake in kilocalories (kcals) and kcals consumed from lipids, protein and carbohydrates will be analyzed using nutritional software (Dietbox Software, Brazil). Thereafter, a food plan will be given to the participants who will follow exactly the same food plan the day before and the day of the experimental sessions. This food plan will not change the composition and amounts of the daily basis food consumption of the participants, but they will be instructed to consume the same meals and the same amounts of food at the same hours of the day during the experimental protocol days, including a pre-session meal composed of 65% carbohydrates, 15% proteins, and 20% lipids one hour before reporting to the gym (~6:30 pm). Frequent text messages will be sent to participants to ensure they followed instructions. Adherence to dietary instructions will be verified by assessing their food record. After the experimental sessions, a standard snack (65% carbohydrates, 15% proteins, and 20% lipids) will be offered, which will be ingested between 9:00 and 9:30 pm at the gym where the sessions will take place, with calories determined from the individual daily needs, plus the estimated net energy expenditure of the session [57]. Participants will be instructed not to consume food after the offered snack and must fast until the morning of the next day to perform the OGTT in a local laboratory.

### Interventions

Participants will be instructed not to perform moderate/high physical activity during the 48 hours that precede the experimental sessions. Frequent text messages will be sent to participants to ensure they follow instructions. Adherence to physical activity instructions will be verified before each session by asking the participants.

#### High-volume session

All sessions will be held at the university facilities and will always be accompanied by the same certified fitness professional. Participants will report to the gym at 7:30 pm, where they will remain at rest until 8:00 pm, only receiving guidance on the exercises to be performed and will respond to the pre-session affection scale (see below in **Subjective measurements**), as suggested by Alves et al [58]. The experimental session will start at 8:00 pm and will be as follows: an initial 5 minute warm-up walking on a treadmill (~3–4 km/h) followed by 7 strength exercises that recruit the major muscle groups, performed in the order presented below: 1 –hex bar squat; 2 –bench press; 3 –leg press; 4 –lat pulldown; 5 –leg extension; 6 –shoulder press; 7 –leg curl. Participants will perform 3 sets with the previously determined 8-RM load, with as many reps per set as they tolerate (until concentric muscular failure–determined as the inability to maintain full range of motion or the inability to maintain tempo (~1:2 sec) for 2 consecutive reps, or by voluntary fatigue of the participant), with a rest of 120 s between sets and exercises. At the end of each set, they will respond to the OMNI-RES scale to ensure that they have reached maximum effort (9 or 10 on the scale). The number of reps performed in each set will be recorded to calculate the total exercise volume-load [59]. Based on pilot studies, sometimes the participant might not be able to complete the first rep of a given set, especially for latter exercises (e.g. leg extension and leg curl). In case that happens, we will not consider that set, will reduce the load by 5–10%, and give them 1 minute to rest after which another attempt will be made. If even after this the participant is unable to complete the first rep of the set, we will consider that the number of reps for that set was 0, and will move on to the next exercise, or finish the session (if this happens during the last exercise, e.g., leg curl). Also based on pilot studies, we anticipate this session will end between 8:45 and 8:55 pm. After that, participants will remain sedentary, answer the feeling, enjoyment, and self-efficacy scales (see below in **Subjective measurements**), and ingest the standard meal described above between 9:00 and 9:30 pm. After an overnight fast, they will report to a clinical analysis laboratory the next day in the morning (between 07:00 and 08:00 am) to perform the OGTT. Thus, the interval between the end of the session and the OGTT will be ~10 to 11 hours.

#### Low-volume session

In this session, all procedures will be identical to the high-volume session, with the exception of the number of sets performed; in this case, only 1 set will be performed in each of the 7 strength exercises. This session will last ~15–20 min. To avoid variations in the time between the end of the session and the OGTT, this session will start between 8:35–8:40 pm so that it ends at the same time as the high-volume session.

#### Control session

In this session, all procedures (including pre-session instructions) will be identical to the high-volume session, with the exception of performing the strength exercises. However, to simulate all other procedures performed in the high-volume session, participants will follow all instructions and, in the gym, will wear the same clothes, sit on the equipment for the same amount of time as the high-volume session, without any reps being performed. Subjective measures and OMNI will also be responded by the participants mimicking the high-volume session.

### Subjective measurements

To verify feeling, the scale described by Hardy and Rejeski [60] and validated to Portuguese by Alves et al [58] will be used. This scale will be answered by the participants before and after the experimental session [58]. To assess enjoyment, the physical activity enjoyment scale (PACES) described by Kendzierski and DeCarlo [61] and validated in Portuguese by Alves et al [58] will be used. To assess self-efficacy, a modified scale proposed by McAuley et al [62] will be used.

### Primary blood outcomes–OGTT-derived indexes

After ~9–10 hours of overnight fasting and ~10–11 hours after each experimental session, participants will report to a local clinical laboratory, and a blood sample will be collected (minute 0). Then, they will ingest 75 grams of glucose in 300 ml of water, and blood samples will be collected every 30 minutes until 120 minutes after glucose ingestion, totaling 5 withdrawals (minute 0, minute 30, minute 60, minute 90, and minute 120). Plasma concentrations of glucose, insulin, and C-peptide (a marker of insulin production) will be analyzed in each sample. With the insulin and glucose results at minute 0 (fasting values), insulin resistance will be calculated using HOMA-IR with the formula glucose (mmol) x insulin (μU/ mL) ÷ 22.5 [63], and insulin sensitivity using the quantitative insulin sensitivity check index [64]. Several insulin sensitivity indexes will be derived from the OGTT data [28], such as the oral glucose insulin sensitivity index [65], the Matsuda insulin sensitivity index [66] and Cederholm’s index [67], muscle insulin sensitivity index [68, 69], glucose-stimulated insulin sensitivity index [21], Gutt index [70], Avignon et al. index [71], Belfiore et al. index [72], Stumvoll et al. index [73], and McAuley et al. index [74], the simple index of insulin sensitivity [75], and as an index of hepatic insulin resistance, the hepatic insulin resistance index [68]. In addition, the glucose, insulin, and C-peptide AUC will be calculated using the trapezoidal method [76].

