Studies that have assessed the acute effects of strength exercise volume on insulin sensitivity are scarce [11]. Reed et al [26] studied 1 or 3 sets (10 exercises, 10 reps, 65% 1 RM), performed in a circuit style program, in normoglycemic women, and found a significant improvement in insulin sensitivity only after the session with higher volume. Unfortunately, the prescription of strength exercise in circuit style prevents inferences for traditional strength exercise. Black et al [27] evaluated 8 exercises performed with 1 or 4 sets, either at 65% 1RM (12–15 reps) or 85% 1RM (6 to 8 reps). The authors observed improvements in insulin resistance in all protocols; but, protocols with single sets showed less effect. However, in that study, the degree of effort in each set was not reported and arguably higher in the high-volume conditions, and as this parameter is suggested as a determinant in the improvement of insulin sensitivity [23], one cannot exclude the possibility this factor played a role in the results observed. Furthermore, Black et al [27] assessed insulin resistance by the homeostasis model assessment of insulin resistance (HOMA-IR), which is more limited than other methods, such as OGTT-derived indexes [28], and more closely reflects hepatic insulin resistance [29]. These few studies in the literature, as well as their limitations, show the need for more research on the effects of strength exercise volume on insulin sensitivity.

Another important point regarding the prescription of strength exercise are the factors that prevent people from regularly engaging in exercise training. When asked about non-adherence to an exercise protocol, the most frequent justification is lack of time [30]. In addition, low self-efficacy (self-perception of the inability to accomplish something) is also one of the reasons people do not exercise frequently [31]. Additionally, positive feelings experienced in response to exercise are important factors for long-term adherence to an exercise program [32, 33]. Therefore, investigating the effect of low- and high-volume strength exercise–which leads to low and high time commitment, respectively [34]–on insulin sensitivity can be beneficial to motivate people who claim not to have time to perform strength exercises and for those who feel that they are not able to or do not experience positive feelings when performing high volumes of strength exercise.

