## Objective

### Primary objective

The primary objective will be to investigate the acute effects of high- and low-volume strength exercise sessions on insulin sensitivity indexes in obese adults.

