Data will be expressed as the mean and standard deviation with a confidence interval of 95%. For the analysis of data normality, we will perform the Shapiro-Wilk test. For normally distributed data, analysis of variance will be used with one source of variation (experimental situation). If a significant main effect was observed, post hoc Tukey test was used. For non-parametric data, the Kruskal-Wallis test was used, or Friedman’s test, when necessary. Effect size was calculated and interpreted as follows: <0.2 = no effect, 0.2–0.49 = low effect, 0.5–0.79 = medium effect, and greater than 0.8 = large effect [81, 82]. The significance level will be 5%. The Prisma program (GraphPad Software, San Diego, CA-USA–version 8.4.0) will be used to analyze the results. The trial will be reported following the CONSORT guidelines [83, 84].

As stated above under **Blinding procedures**, the researcher responsible for data analysis (the statistician) will be blinded for group allocation. For that, a collaborator outside the research team will double enter data coded for allocation into a computer in separate spreadsheets so that the researcher responsible for data analysis can assess data without having access to information about the allocation. Allocation will only be revealed after statistics are run. In case there are doubts about data entry (missing values, or values outside the reference range), the researcher responsible for data analysis will contact the collaborator outside the research team responsible for double entry of the data to check accuracy. There will be no interim analysis.

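### No single primary outcome: 14 insulin indexes and 3 AUCs share primary rank under one 5% level, with no rule for what the trial concludes

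*Protocol article*

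**What the plan says.** The primary objective (Protocol article, Primary objective) is the effect of the two exercise volumes "on insulin sensitivity indexes in obese adults", in the plural and with none singled out.

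The outcomes stand under the heading "Primary blood outcomes–OGTT-derived indexes". That section contains:

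- two fasting indexes: HOMA-IR ("insulin resistance will be calculated using HOMA-IR with the formula glucose (mmol) x insulin") and the quantitative insulin sensitivity check index (QUICKI);
- twelve named OGTT indexes, introduced by "Several insulin sensitivity indexes will be derived from the OGTT data [28], such as the oral glucose insulin sensitivity index": oral glucose insulin sensitivity, Matsuda, Cederholm, muscle, glucose-stimulated, Gutt, Avignon, Belfiore, Stumvoll, McAuley, the simple index and the hepatic insulin resistance index;
- three areas under the curve: glucose, insulin and C-peptide.

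The next section, Secondary blood outcomes, contains only the lipid profile, so it demotes nothing from this list.

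Data analysis gives one level for everything ("The significance level will be 5" per cent), an ANOVA or rank test per variable, and Tukey after a significant main effect. Sample size uses an effect size of 0.6 without saying which outcome it refers to.

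**The concern.** A trial's primary outcome is what its conclusion and its sample size rest on. Here the label covers a list of 17 quantities that is not closed. Followed as written, any one of them could be reported as the positive primary result once allocation is revealed.

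The list also mixes quantities that the article itself does not treat as equivalent. The Introduction faults an earlier study of exercise volume for relying on HOMA-IR, "which is more limited than other methods, such as OGTT-derived indexes", and notes that it mainly reflects hepatic resistance. HOMA-IR then appears in the primary section beside separate muscle and hepatic indexes. If these point in different directions, nothing in the article says what the trial has found. The article describes the existing literature as conflicting, and an unranked list risks adding another ambiguous result.

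**Working it through.** **1. Count.** Fasting indexes 2 + named OGTT indexes 12 = 14 indexes. Adding 3 AUCs gives 17 outcomes.

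**2. The plan's own figure.** Inputs from Sample size: one-way ANOVA, effect size 0.6 (read as Cohen's f, an assumption), alpha 0.05, target power 0.9; three conditions from Study type and design. Power comes from the noncentral F distribution with λ = f² × N, where N is the total number of observations.

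- 13 per condition: N = 39, power 0.906.
- 14 per condition: N = 42, λ = 0.36 × 42 = 15.12, degrees of freedom 2 and 39, power 0.928.

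The second line matches the stated 14 and 0.93. This is power for one outcome at 5%.

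**3. False positives if each outcome is tested at 5% and the sessions do not differ.** The expected number of false positives is 17 × 0.05 = 0.85, whatever the correlation. The chance of at least one under independence is 1 − 0.95^k:

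- k = 17: 1 − 0.95^17 = 58.2%
- k = 14: 1 − 0.95^14 = 51.2%
- k = 12: 1 − 0.95^12 = 46.0%

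Independence cannot hold here, and the article gives no correlations between outcomes. A common correlation was therefore assumed, and three-condition repeated-measures ANOVAs with n = 14 were simulated (6,000 trials per setting for 17 and 14 outcomes, 20,000 for 12):

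| Assumed correlation | 17 outcomes | 14 indexes | 12 OGTT indexes |
|---|---|---|---|
| 0.5 | 40% | 37% | not run |
| 0.7 | 29% | 27% | 25% |
| 0.8 | 23% | 21% | 20% |
| 0.9 | 16% | 14% | 14% |
| 0.95 | 12% | 11% | 11% |

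Simulation error is about half a percentage point. Even at correlation 0.95, the 17-outcome figure is 0.12 / 0.05 = 2.4 times the nominal level.

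Tukey does not change this. It protects the three pairwise session contrasts within one outcome, not the choice among outcomes.

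**4. Can the indexes disagree?** Strengths gives correlations of 0.61 and 0.96 between the indexes and the clamp. If both came from one population (an assumption), two indexes at those ends could correlate with each other only between 0.61 × 0.96 ± √[(1 − 0.61²)(1 − 0.96²)] = 0.586 ± 0.222, that is, between 0.36 and 0.81. Discordant indexes are a realistic prospect.

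**5. Would a later adjustment repair it at this sample size?** With Bonferroni over 17, alpha per outcome is 0.05 / 17 = 0.0029. On the inputs of step 2, power at 14 per condition falls from 0.93 to 0.63, and 22 per condition are needed to pass 0.90 (0.913). Bonferroni is conservative for correlated outcomes, so this is a worst case. With one named primary outcome at 5%, the stated 14 and 0.93 are unaffected.

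**The case against.** Five points can be made for the plan.

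- **The primary family may be narrower.** The heading refers to OGTT-derived indexes, HOMA-IR and QUICKI use only fasting values, and the AUCs are added at the end and are not indexes. On that reading 12 outcomes are primary, and the complaint about HOMA-IR's rank falls away. The text does not settle this, because only lipids are called secondary. Twelve unranked outcomes still leave the same gap, with 25% to 11% at correlations of 0.7 to 0.95.
- **58% overstates the risk.** This stands in part. All outcomes are computed from the same five blood samples per session, so 58% is a ceiling and the correlated figures are the ones to use. Those rest on an assumed correlation.
- **Testing each outcome at 5% is inferred.** This is correct: the article states one level and no adjustment across outcomes, but does not go index by index. An adjustment could sit in an analysis plan that is not shown. The choice of primary outcome could not be left there in the same way: it is a protocol decision, and the article does state a primary set.
- **The registry record or full protocol may name a lead outcome.** Neither is available here. The claim is limited to what this article fixes.
- **There are safeguards.** The analyst is blinded, confidence intervals and effect sizes are planned, and results will be published whatever their direction. Because the indexes are named, an omitted one would be noticed. These measures restrain selective reporting, but they neither control error across outcomes nor resolve discordant indexes.

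**Conclusion.** The concern holds. The article gives primary rank to an open list of 14 indexes and 3 AUCs. It names no lead outcome, testing order or rule for a positive trial, and it sizes the study on an effect that belongs to no stated index.

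If every outcome is tested at 5%, the chance of at least one false positive is about 12% to 29% for assumed correlations of 0.95 down to 0.7, with 58% as the independence ceiling. The percentages depend on the assumed correlation and on the inference about testing. The missing primary outcome depends on neither. This needs to be corrected before data are seen, since a choice made afterwards would not be credible.

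**What to change.** Name one OGTT-derived index as the sole primary outcome and rest both the sample size and the trial's conclusion on it. The Matsuda index is one example: it is already listed and can be computed from the planned samples. Nothing in the article makes it the only possible choice.

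Move the remaining indexes, including HOMA-IR and QUICKI, and the three AUCs to secondary or supportive status, reported with estimates and confidence intervals and without confirmatory claims. Replace the open-ended wording with a closed list.

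If the investigators prefer a small co-primary set or a fixed testing order, that can also work, provided the error control and the sample size are set out for it.

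The cost is wording plus an ethics submission and registry update, the route that Ethics approval already foresees. No additional samples, visits or participants are needed with a single primary outcome. The investigators give up the option of presenting a different index as the primary result.
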